### Data collection

The data collection will occur at the urogynecology outpatient clinic located in the Maternity Hospital Januário Cicco School from the Federal University of Rio Grande do Norte, Natal, Brazil.

### Data monitoring

This study will not involve participants in life-threatening or harmful interventions; therefore, it will not be necessary to create a data security monitoring board.

### Harms

Adverse events will be carefully monitored during all study phases by asking the participants during and after each session if there is any adverse event related to pelvic floor muscle training and photobiomodulation. We will register and analyze any adverse event during the research period. Immediate interruption will occur in case of any risk. It is emphasized that the risks of this project are minimal, such as musculoskeletal pain or fatigue, itching, tingling, and burning sensations. The risks may vary depending on the group to which the volunteer is allocated. If any women withdraw, we will perform an intention-to-treat analysis or imputation data. In case of any harm related to the intervention, the researchers will provide all the necessary support.

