**Methods:**

It is a randomized, controlled, double-blind clinical trial protocol study that will include women experiencing genitourinary symptoms related to menopause, sexually active, never practiced pelvic floor muscle exercise or photobiomodulation treatment, and do not use hormone replacement therapy for at least 3 months. The randomization will allocate the women to three groups: PFMT group, PFMT associated with active intracavitary photobiomodulation group, and PFMT associated with sham intracavitary photobiomodulation group. A total of 16 sessions will be conducted twice a week. The assessments will occur before interventions, after the sixteenth session, and 1 month after the sixteenth session (follow-up). The evaluation will include the pelvic floor muscle vaginal manometry as the primary outcome. Also, the international consultation on incontinence questionnaire—short form, the female sexual function index, the Utian Quality of Life scale, the patient global impression of improvement, the modified Oxford scale, and the vaginal health index will be the secondary outcomes.

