### Non-adherence criteria

We will consider as non-adherence criteria any report of unbearable pain during the gynecological evaluation, more than 20% absences during the intervention period, or those who withdraw their consent to participate in the research.

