### Interventions

The researchers will assign the women to one of the three groups: PFMT group, PFMT associated with active intracavitary photobiomodulation group, or PFMT associated with sham intracavitary photobiomodulation group. The exercise program will last 50 min per session, a 5-min warm-up, and a 45-min exercise, including the rest time between them. A total of 24 sessions will be conducted twice a week. Figure 1 illustrates the study flow diagram.

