### Participants timeline

Initially, the included women will provide the information requested in the evaluation form, questionnaires, Oxford Modified Scale, vaginal manometry, vaginal health index, and vaginal pH. The midpoint evaluation will occur immediately after the twelfth session. The final evaluation will be conducted immediately after the twenty-fourth intervention. Another evaluation will take place 1 month after the last intervention (follow-up). The evaluations will follow the same protocol by a blinded evaluator. See the SPIRIT diagram (Fig. 5).

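### The Harms section promises to capture any adverse event in every phase, but its only stated method asks at sessions about events the woman links to treatment

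*Protocol article*

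**What the plan says.** The Harms section opens with a broad statement of scope: "Adverse events will be carefully monitored during all study phases". The same sentence then says how this is done, "by asking the participants during and after each session", and what is asked: "if there is any adverse event related to pelvic floor muscle training and photobiomodulation". The next sentence returns to the broad scope, with no limit to related events: "We will register and analyze any adverse event during the research period". The section also lists the expected risks (among them burning, itching, tingling and musculoskeletal pain), calls them minimal, and says that they may differ by group.

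Sessions end with the last intervention. Participants timeline then adds one more contact: "Another evaluation will take place 1 month after the last intervention (follow-up". The evaluation content described under Outcomes and Participants timeline consists of manometry, questionnaires, the modified Oxford scale, the vaginal health index and pH. No adverse-event enquiry is listed there.

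A neighbouring section, Non-adherence criteria, counts "any report of unbearable pain during the gynecological evaluation" among its criteria. The Harms section does not mention that event.

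**The concern.** Scope and method disagree within one short section. A site following the stated method would ask a restricted question, at sessions, and could believe that it had met the promise to register everything.

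Two things are at stake. The first is completeness. The expected harms of burning, itching and pain overlap with the condition itself, which the Introduction describes in terms of dryness, vulvovaginal discomfort and painful intercourse. A woman with new burning may put it down to menopause and answer no to a question about related events.

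The second is the comparison between arms. If reporting passes through the woman's own attribution, and the grounds for attribution differ by arm, the reported difference mixes what happened with what women believe. This matters because the Discussion says that no protocol or intervention for this combination exists in the literature, and the article calls the study preliminary and exploratory of feasibility. Its harms data should therefore be usable.

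**Working it through.** The plan gives no figure on this point, so the check is mainly a comparison of statements.

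**1. Content.** Declared: every adverse event is registered and analysed (Harms). Stated method: women are asked about events related to the training and the light (Harms). An event that the woman considers unrelated lies inside the declared scope and outside the question.

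**2. Time.** Declared: all phases of the study. Stated method: enquiry tied to sessions. The midpoint and final evaluations in Participants timeline follow directly on a session, so the session enquiry reaches that far. The follow-up month has no sessions, and the 1-month visit has no stated enquiry.

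Share of time after the first session without a stated enquiry = F / (T + F), where F is the follow-up month and T the treatment period.
- F: 1 month, taken as 30.4 days; 30.4 / 7 = 4.34 weeks.
- T from the Abstract: "A total of 16 sessions will be conducted twice a week", so 16 / 2 = 8 weeks. Share = 4.34 / 12.34 = 35%.
- T from Interventions: "A total of 24 sessions will be conducted twice a week", so 24 / 2 = 12 weeks. Share = 4.34 / 16.34 = 27%.

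The two session counts contradict each other and must be reconciled. That is a separate matter, and here it only moves the share between these two values.

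**3. Attribution by arm (Interventions).**
- PFMT alone: no probe is used, so there is no device to which a symptom can be attributed.
- PFMT with active light: probe inserted and on.
- PFMT with sham: probe inserted but off, with women wearing glasses so that they do not notice. They may attribute symptoms to a device that emits nothing.

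Let E be the true event rate in an arm and p the probability that an event is reported. The reported rate is E × p. The ratio of reported rates between arms 1 and 2 is (E1 × p1) / (E2 × p2), which equals E1 / E2 only if p1 = p2. A question that depends on attribution gives p a reason to differ by arm.

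**4. What cannot be computed.** The article gives neither E nor p, so no number of missed events follows from it. Arm size does follow: 42 women at 1:1:1 is 42 / 3 = 14 per arm. With no events in an arm, the exact two-sided 95% upper limit is 1 − 0.025^(1/14) = 23.2% (one-sided: 1 − 0.05^(1/14) = 19.3%). This shows how little 14 women can say about harm. It does not measure the present problem, because it would be the same under any wording of the question.

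**The case against.** The strongest reply is that the commitment to register every event stands in the text, and that one sentence in indirect speech in a journal article is not the case report form. Volunteered reports and assessor observations can be registered. The 1-month visit exists, and its instruments touch on symptoms: the FSFI has a discomfort/pain domain, the PGI-I runs to very much worse, and the vaginal health index covers epithelial integrity. The full protocol may hold more.

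Much of this stands, and it rules out several stronger readings that a reader might infer:
- That events in the follow-up month will be missed. The article does not say so, since they could be volunteered at the 1-month visit. It supports only that no stated enquiry elicits them.
- That the question is leading. The exact wording is not given. The article shows only that the enquiry is restricted to related events.
- That unbearable pain at an evaluation is kept out of adverse-event recording. It is classed under non-adherence, but nothing excludes it from being registered as well. It could also arise at baseline, before any treatment.
- That the lack of a monitoring board rests on under-counted events. Data monitoring bases that decision on the nature of the interventions, not on event counts from this trial.

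The reply does not remove the mismatch itself. The article does not stay silent on elicitation and leave it to a fuller document. It states a method, in the same sentence as the broad scope, and the two do not agree. Outcome questionnaires are no substitute for asking about adverse events. An open question would not remove sham women's beliefs about the device, but it would stop those beliefs from deciding what is reported.

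**Conclusion.** The point holds as an internal contradiction in the Harms section: the promised scope (every event, every phase) is not delivered by the one stated method (related events, at sessions). If the method is followed as written, reporting depends on each woman's attribution, which can differ by arm and is hard when harms resemble the presenting condition. The follow-up month, about 27% to 35% of the time after the first session, has no stated enquiry.

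The conclusion assumes that the stated method is the one used; a fuller protocol could already correct it. That attribution differs by arm is a reasoned expectation, not something the article shows. The consequence is confined to the completeness and comparability of the harms data. It is worth correcting because correction is cheap, but it is not a threat to the primary analysis.

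**What to change.** Align the method with the promise already made:
- In all three arms, ask one open, attribution-neutral question, for example whether there has been any new or worse health problem since the last contact. Ask it at every session and every existing evaluation, including the 1-month visit.
- Record every event whatever its presumed cause. State that unbearable pain at an evaluation is also recorded as an adverse event, leaving its place among the non-adherence criteria as it is. Report all events by arm.
- Have relatedness judged afterwards by an existing team member who does not assess outcomes. The blinded assessor should not do this, because accounts of a probe, or of none, could reveal the allocation. The same applies to who puts the question at evaluations: where possible, someone other than the assessor, or a written form that the assessor does not read.

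The cost is a change of form wording, one question at visits that already take place, and some added trivial events to record. No extra visits or staff are needed, and no dose, schedule or stopping rule changes.

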### Ethics and dissemination

The study will follow the Standard Protocol Items: Recommendations for Interventional Trials, Declaration of Helsinki, and resolution 466/12 of the National Health Council. The Ethics Committee of the Federal University of Rio Grande do Norte approved the study (n° 6.038.283). Also, The Brazilian Registry of Clinical Trials (ReBEC) registered the protocol (n° RBR-5r7zrs2). All the data will be stored at the physiotherapy department of the Federal University of Rio Grande do Norte with the principal investigator for 5 years, then they will be discarded.

The participants will be informed about the aims and procedures of the research. They will participate voluntarily, as determined by the 466/12 resolution of the National Council of Health. After that, if agree to participate, they will sign the informed consent form. Any personal information related to the participation in the study will not be shared during or after the study. After finishing the participation, the women randomized into the sham group will be invited to receive the photobiomodulation.

## Discussion

This study protocol presents an innovative and feasible associated strategy to generate clinical improvements in women affected by urinary and sexual dysfunctions caused by GSM. In the literature, there is no protocol or intervention for using PFMT associated with photobiomodulation to treat women affected by urinary and sexual dysfunctions caused by GSM. So, it is possible that the association of PFMT with photobiomodulation might potentiate the improvements.

Although PFMT to treat women affected by GSM generates an increase in blood flow, speed of pelvic floor relaxation after a contraction, an increase of strength, a decrease in the tonus, and skin elasticity improvements (Mercier et al., 2020), the evidence reporting clinical improvements after PFMT for women affected by GSM are biased and scarce (Mercier et al., 2020, 2019). Photobiomodulation is an intervention used to treat several conditions, such as sexual dysfunction (Frederice et al., 2022), vulvovaginal disorders (Forret et al., 2023), and UI (De Marchi et al., 2023). There is evidence showing that photobiomodulation in the vaginal region increases collagen production, oxygenation, tissue tensile strength, vasodilator, accelerates wound healing, and reduces pain (Frederice et al., 2022; De Marchi et al., 2023). In this sense, photobiomodulation also might be a feasible strategy to treat women affected by urinary and sexual dysfunctions caused by GSM.

The association of photobiomodulation with other techniques, such as pilates (De Marchi et al., 2023) and stretching, (Frederice et al., 2022) has already been studied and presented improvements for pain, sexual dysfunction, and strength in women with pelvic and urinary dysfunctions (De Marchi et al., 2023; Forret et al., 2023). Considering these assumptions, due to women affected by GSM presenting alteration in the genitourinary tract, such as urinary and sexual dysfunctions (Palacios et al., 2017), it is highly possible that photobiomodulation potentiates the effects of PFMT in the genitourinary tract.

This protocol presents some limitations and strengths that must be acknowledged. There will be no sensor to confirm if the women are performing efficient pelvic floor muscle contractions during interventions. However, the researcher will stimulate the pelvic floor contraction during the whole session. Also, we will use validated, easy-to-use, and cheap instruments with clinical applicability to evaluate the effects of the treatments. Lastly, a long-term follow-up could demonstrate if the effects of the intervention would last longer.

## Conclusion

PFMT associated with photobiomodulation protocol is expected to amplify the effects of isolated PFMT in women experiencing GSM accompanied by urinary and sexual dysfunctions. Also, we project that this combined protocol mirroring clinical practice is feasible for women. This preliminary study intends to explore the feasibility and initial trends for PFMT associated with photobiomodulation.

## Supplemental Information

10.7717/peerj.17848/supp-1Supplemental Information 1Test instruments information.

10.7717/peerj.17848/supp-2Supplemental Information 2Global impression questionnaires for incontinence.

10.7717/peerj.17848/supp-3Supplemental Information 3Oxford scale article.

10.7717/peerj.17848/supp-4Supplemental Information 4SPIRIT Checklist: Recommended items to address in a clinical trial protocol and related documents.
